### Procedure

#### Conventional care group

Participants randomly allocated to the conventional care group will continue to manage their heart health as directed by their primary care doctor or by their own cognisance. This group will not receive any additional intervention as a result of participation in the study. However, they will be contacted by telephone 2–3 weeks after baseline assessment to confirm their three month assessment appointment. In addition, each participant's general practitioner (GP) and cardiologist will be mailed a courtesy letter following baseline assessment and a risk factor summary with recommendations for discussion regarding long-term risk factor management following the final 12 month assessment.

#### Modular group

Participants randomly allocated to the modular group will manage their heart health by participation in modular guided self-choice management of heart disease. That is, participants will participate in risk factor modules of their choice, with the exception of the mandatory blood cholesterol module, strive to achieve mutually-agreed goals and make choices about risk factor reduction interventions based on their own circumstances. Following baseline assessment, the consultation will be extended by approximately 30 minutes for selection of modules, goal setting and shared decision making about risk factor interventions.

The risk factor modules consist of cholesterol-lowering, BP management, smoking cessation and physical activity. All participants will participate in the cholesterol-lowering module and where applicable, participants can also choose up to two other modules depending on their individual risk factor assessment and personal preference. Therefore, all participants will participate in a minimum of one risk factor module and a maximum of three modules at any one time.

The mandatory cholesterol-lowering module involves pharmacological intervention in consultation with the primary care doctor as well as education and empowerment through information and support about individual and nationally recommended cholesterol levels. The three optional modules involve choice of intervention including; following medical advice; participating in a structured program (individual or group); participating in a home program; or self-help. All risk factor modules will be resourced and delivered separately among the primary care doctor, the local area health service, the local community and the participant. Participants in the modular group will receive a resource package including appropriate information leaflets which contain guidelines and information about the module and contact information for community heart health programs. The leaflets have been developed and pilot tested, for validity, by health professionals and consumers.

For each risk factor module, a three month objective goal will be set based on shared decision-making. The mutually-agreed goal will be based on the each participant's risk factor profile, social factors, commitments and personal preference. Participants will also asked to rate their confidence in achieving the set goal on a visual analogue scale from 1–10. Each risk factor baseline level, mutually agreed goal, time frame and confidence rating will be recorded on the information leaflet.

All participants in the modular group will also be "coached" using a previously published model [38]. The coaching model is a five stage cyclic process and involves assessing understanding, providing education, assertiveness training and reassessment. In this study, the first coaching session will be conducted during the initial face-to-face shared decision making, goal setting session. Participants will then be coached over the telephone on up to four further occasions, depending on goal achievement, during the following three months depending on need. Once each risk factor goal is achieved, no further coaching is required. All coaching will be conducted by a researcher who has been trained by the original coach study coordinator. During each coaching session individual's knowledge of their risk factors and personal goals will be identified and participation in the module will be established and recorded.

Communication between the study coordinator, the participant and health professionals involved and community services will be facilitated where possible. Each participant will also be encouraged to communicate openly about their goals and modules with their local doctor and cardiologist. During the course of the study, participants identified as being clinically depressed, according to their CDS, are to be offered an appointment with a clinical psychologist specialising in heart disease. For each participant, their GP and cardiologist will be sent a comprehensive letter outlining the participant's risk factors, goals and chosen modules. Following the final 12 month assessment, all participants and their doctors will also receive a cardiac risk factor summary and recommendations for discussion regarding long term risk factor management. By facilitating communication, it is anticipated that each participant receives a coordinated multidisciplinary approach to their own risk factor management based on need and situation.

#### Standard rehabilitation group

Participants who volunteer for the standard rehabilitation group will attend the hospital-based outpatient cardiac rehabilitation program. This rehabilitation program includes twice weekly group hospital-based exercise classes for six weeks and weekly education sessions. The exercise program is supervised by a clinical nurse specialist and a physiotherapist. The exercise sessions are generally of 45 minutes duration and include a 10 minute warm up and cool down and approximately 30 minutes of cardiovascular and resistance exercise stations. These stations include leg press, treadmill walking, stair climbing, knee extension weights, stationary cycling and gentle upper limb weights. Each station is conducted for 3 minutes and patients rotate around the room from station to station with a 2 minute rest between stations. Exercise intensity is based on rating of perceived exertion (RPE) at a moderate level (3–4) on the modified RPE scale [39].

The education sessions, include general information about heart disease and associated risk factors, two sessions by a pharmacist about medications, two sessions about dietary advice by dietitian (one theoretical and one practical session), two sessions from a clinical psychologist and one session about exercise by a physiotherapist. Participants will be encouraged to attend two exercise sessions per week and all the educational sessions if possible. There is no transport available for travel to and from the sessions however, parking is available in the hospital car-park at each patient's expense. Similar to the conventional care group, the standard rehabilitation group will not receive any additional intervention as a result of participation in the study. However, all participants will be contacted by telephone 2–3 weeks after baseline assessment to confirm their three month appointment. In addition, each participant's GP and cardiologist will be mailed a courtesy letter following baseline assessment and a risk factor summary with recommendations for discussion regarding long term risk factor management following the final 12 month assessment.

### Sample size

Participant numbers required for each group have been calculated to detect a 0.5 mmol/L reduction in TC with 80% power. The LIPID study of 9014 subjects with CHD reported a mean TC of 5.6 (± 0.7) mmol/L [40] and it has been assumed that a clinically significant change in TC would be 0.5 mmol/L. Therefore, to achieve power of 80% to detect a change of 0.5 of a SD unit, using a two-tailed test with an alpha level of 0.05 and allow for 10% loss to follow-up, it was calculated that 72 participants per group will be recruited.

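### The sample size equates 0.5 mmol/L with 0.5 SD although the only quoted SD is 0.7 mmol/L, so 72 per group gives about 98% power for the stated target, not 80%: a conservative error in the power statement

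*Protocol article*

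**What the plan says.** Everything relevant stands in one paragraph of the protocol article, under Sample size.

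- Target: the numbers per group were "calculated to detect a 0.5 mmol/L reduction in TC with 80% power".
- Variability: a large earlier study of 9014 patients with coronary disease is cited for a "mean TC of 5.6 (± 0.7) mmol/L". No other SD is given, and none for change from baseline.
- Relevance: "it has been assumed that a clinically significant change in TC would be 0.5 mmol/L".
- Calculation: introduced as a consequence of the above, it is framed "to achieve power of 80% to detect a change of 0.5 of a SD unit", "using a two-tailed test with an alpha level of 0.05", with an allowance of 10% for loss. The result is 72 per group.

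**The concern.** The paragraph moves from 0.5 mmol/L to 0.5 SD as if one followed from the other. That holds only if one SD is 1.0 mmol/L, and the SD printed beside the target is 0.7. At least one of target effect, SD and power therefore cannot be what the calculation used.

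This is the only sample-size justification in the article. Cholesterol is one of the modifiable risk factors listed under Outcome measures, and the Discussion makes the magnitude of those risk factors the primary outcome. A reader who uses the paragraph to judge a TC result would take the trial to be sized at 80% for 0.5 mmol/L. The same reader could not tell whether the planners meant a smaller target (0.35 mmol/L) or a larger SD (1.0 mmol/L). Under the first the trial has ample margin for 0.5 mmol/L; under the second it has none.

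**Working it through.** **Inputs, all from Sample size:** difference 0.5 mmol/L; SD 0.7 mmol/L; standardised effect 0.5; power 80%; two-sided alpha 0.05; loss 10%; 72 per group.

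**Assumptions:** a comparison of two means in equal groups, and ± 0.7 read as an SD. As a standard error from 9014 subjects it would imply an SD of 0.7 × √9014 ≈ 66 mmol/L, which is not plausible.

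**Formula.** With d = difference / SD, the normal approximation is n per group = 2 × (1.960 + 0.842)² / d² = 15.70 / d². The t test adds about one per group. Recruited number = n / (1 − 0.10).

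**1. Reproduce the plan's figure (d = 0.5).**
- Normal approximation: 15.70 / 0.25 = 62.8, so 63; 63 / 0.9 = 70.
- t test: 63.8, so 64; 64 / 0.9 = 71.1, so **72**, an exact match.

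The 72 therefore comes from 0.5 SD.

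**2. Convert between the two effects at SD 0.7.**
- 0.5 mmol/L = 0.5 / 0.7 = 0.714 SD.
- 0.5 SD = 0.5 × 0.7 = 0.35 mmol/L.

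**3. Size for the stated target (d = 0.714).**
- Normal approximation: 15.70 / 0.510 = 30.8, so 31; 35 with loss.
- t test: 31.8, so **32**; 32 / 0.9 = 35.6, so **36** with loss, half of 72.

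**4. What 72 recruited delivers.** After 10% loss, 72 × 0.9 = 64.8, so 64 to 65 per group are analysed.

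| SD (mmol/L) | Difference (mmol/L) | Power, 64 analysed per group (t test) |
|---|---|---|
| 0.7 (quoted) | 0.35 | 80.1% |
| 0.7 (quoted) | 0.50 | 98.0% |
| 1.0 (not in the article) | 0.50 | 80.1% |

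Power for 0.5 mmol/L at SD 0.7 is 98.1% with 65 analysed and 98.9% with all 72.

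**5. Other routes to 72 from 0.5 mmol/L and SD 0.7** (normal approximation).
- One-sided test: 25 per group before loss.
- Bonferroni for three pairwise comparisons: 42, or 47 with loss.
- SD of change with zero correlation between baseline and follow-up: 0.7 × √2 = 0.99; 62, or 69 with loss.

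Only the last comes close. The article states no such assumption and describes the calculation as 0.5 of an SD.

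**The case against.** The strongest reply is that nothing in the trial is harmed. At the only SD in the article the mistake is on the safe side: 98% power where 80% was promised. The basis of the 72 can be recovered from the paragraph, and the sample size, allocation and test all stay as they are. A size above the minimum for TC is not plainly wasteful either, because TC is one of six modifiable risk factors measured. This stands, and it limits the severity. It does not rescue the wording: the article does not say the number was raised for the other risk factors, and the power it attaches to 0.5 mmol/L is wrong on its own inputs.

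Two stronger readings are tempting, and the document supports neither.

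- *The trial is underpowered.* A reader who sees that the stated 80% is wrong might infer a shortfall. For 0.5 mmol/L that would require an SD above 1.0 mmol/L. The article gives no such value, so any lower power figure would rest on an assumed SD.
- *The error makes the trial declare significance for trivial differences.* With 64 per group at SD 0.7 the smallest difference reaching p < 0.05 is 1.979 × 0.7 × √(2/64) = 0.245 mmol/L. A trial sized correctly for 0.5 mmol/L, with 32 per group, also reaches significance below its target: 1.999 × 0.7 × √(2/32) = 0.35 mmol/L. Only the shift from 0.35 to 0.245 belongs to this error.

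**Conclusion.** The inconsistency is real, and nothing elsewhere in the article resolves it. The 72 per group is the answer for 0.5 SD. It is twice the 36 that 0.5 mmol/L at the quoted SD requires, and power for that target is about 98%, with 80% reached at about 0.35 mmol/L.

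The direction is conservative, and no shortfall is shown. The one caveat is that if the planners had SD 1.0 mmol/L in mind, the two targets coincide and 80% is correct, but the quoted 0.7 is then not the planning SD and there is no spare margin. The document does not show which was meant.

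Severity is moderate: the stated basis is false as written, but recruitment and analysis are unaffected. The figures rest on a two-sided 5% two-sample t test, equal groups and 10% loss.

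**What to change.** Keep 72 per group and restate the basis in one of two ways. The sponsor must choose, since only the planners know which effect was intended.

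- If 0.7 mmol/L is the planning SD: *With an SD of 0.7 mmol/L, 64 evaluable participants per group give 80% power for a difference of 0.35 mmol/L (0.5 SD) and about 98% power for 0.5 mmol/L; 72 per group are recruited to allow for 10% loss.*
- If 0.5 mmol/L was meant to equal 0.5 SD: state that an SD of 1.0 mmol/L was assumed, give the reason, and stop presenting 0.7 as the planning SD. The 80% power for 0.5 mmol/L then stands.

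The cost is the rewording of one paragraph. Recruitment, allocation and the planned analysis do not change.

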### Data analysis

Data will be analysed by intention-to-treat using SPSS for Windows (Version 12.01) and will be presented as mean and standard error of the mean or proportions. Differences in outcome measures, between and within groups, will be compared using repeated measures ANOVAs for continuous variables and either χ^2 ^tests or Fishers exact tests, as appropriate, for proportions of categorical variables. Two tailed p values of < 0.05 will be considered significant.

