### Group allocation

For the standard cardiac rehabilitation group, participants will be consecutively recruited prior to commencement of outpatient cardiac rehabilitation. Patients who are eligible for but not participating in cardiac rehabilitation will be randomly allocated to either their modular or conventional care group immediately following completion of the baseline assessment. Therefore, the researcher conducting each baseline assessment will be blinded to group allocation. Prior to study commencement, a computer-generated allocation sequence will be constructed using randomly permutated blocks [25]. An individual not involved in the study recruitment, data collection or analysis will produce consecutively numbered sealed opaque envelopes containing each participant's allocation. Following baseline assessment, the researcher will select the next consecutively numbered envelope and open it to reveal the allocated group. They will then notate the unique patient identifier on the front on the participants cover sheet. Therefore, group allocation will be concealed from the researcher conducting baseline assessments.

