### Outcome measures

Assessments will be conducted in the hospital consulting rooms or in the participant's home, if they are unable to travel to the hospital. Demographic, subjective and objective information will be obtained during face-to-face assessments at baseline, three and 12 months. Information will include past history, nature of ACS, family history, age, medications and dose, presence of other cardiovascular disease and the nature and date of any revascularisation. In addition, contact details for each participant, their general practitioner and their cardiologist will be documented.

At three and 12 month follow-up, all baseline measures will be repeated during face-to-face assessments by a researcher blinded to group allocation. Additional collected information will include – details of unplanned hospital admissions, medications and doses along with details of any health interventions undertaken by the participant pertaining to their heart health, such as visits to the GP and attendance at community programs. For participants in the standard rehabilitation group, details of participation in the cardiac rehabilitation program will also be recorded such as duration and attendance at exercise and education sessions.

Modifiable risk factors to be measured are serum cholesterol, BP, smoking status, physical activity, overweight and depression. Lipids and substrates will be measured on a fasting blood sample within two weeks of assessment date. Participants will be referred to local pathology clinics by their primary care doctor and will visit the clinics by their own arrangement. Blood samples will be analysed for determination of total cholesterol (TC), low density lipoprotein cholesterol (LDL-C), high density lipoprotein cholesterol (HDL-C) and triglycerides (TG). Repeat blood tests will be carried out at the same pathology clinic wherever possible.

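### Repeated measures ANOVA, read naturally, treats the pre-randomisation baseline as an outcome; it has less power than a baseline-adjusted follow-up analysis and, in classical form, drops participants with one missing visit

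*Protocol article*

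**What the plan says.** The Data analysis section names the method for every continuous outcome: "Differences in outcome measures, between and within groups, will be compared using repeated measures ANOVAs for continuous variables". The sentence before it sets the analysis principle: "Data will be analysed by intention-to-treat using SPSS for Windows (Version 12.01". The section names no baseline covariate, does not say which ANOVA term tests the treatment, and gives no rule for missing visits.

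Outcome measures sets the visits: "Demographic, subjective and objective information will be obtained during face-to-face assessments at baseline, three and 12 months". It adds: "At three and 12 month follow-up, all baseline measures will be repeated during face-to-face assessments by a researcher blinded to group allocation". Under Group allocation, participants are "randomly allocated to either their modular or conventional care group immediately following completion of the baseline assessment", so the baseline value always precedes randomisation.

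Sample size plans 72 per group for 80% power to detect 0.5 SD, "using a two-tailed test with an alpha level of 0.05", and says that the number is to "allow for 10% loss to follow-up".

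**The concern.** The article does not list the levels of the repeated factor. With within-group comparisons, three visits and no covariate, the natural reading is that baseline, 3 and 12 months are all response levels. Three things follow.

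- **Main effect.** The between-group effect averages one visit that treatment cannot have influenced with two that it can. An effect present at both follow-ups is reported at two thirds of its size.
- **Group-by-time.** This test does address treatment, but it is an omnibus test on 2 degrees of freedom. It uses baseline by differencing instead of by regression, which costs power when visits are only moderately correlated.
- **Missing visits.** Classical repeated measures ANOVA needs a value at every visit. A participant seen at 3 months but not at 12, or with one missed blood test, contributes nothing.

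At stake are precision and the use of randomised participants whose data have been collected. The Discussion names the modifiable risk factors as the primary outcomes, so the method governs the continuous primary outcomes as well as cholesterol.

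**Working it through.** **Inputs from the Protocol article.** Two-sided alpha 0.05; power 80%; effect 0.5 SD; 10% loss; 72 per group; 0.5 mmol/L and SD 0.7 mmol/L for total cholesterol; three visits.

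**Assumptions.** The correlation r between visits is not given, so it is varied from 0.3 to 0.8. Compound symmetry, unit SD and the same effect d at 3 and 12 months are assumed.

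**Step 1: reproduce the plan's figure.** A two-sample t-test with d = 0.5, alpha 0.05 and 80% power needs 63.8, so 64 per group. 64/0.9 = 71.1, rounded up to 72. The plan's number reproduces as a simple two-group comparison with the 10% loss included.

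**Step 2: effect and variance for each analysis.** Every test except group-by-time uses noncentrality effect/√(2 × variance/n), with n = 64 per arm.

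| Test | Effect | Variance per participant |
|---|---|---|
| 12-month t-test, no baseline | d | 1 |
| ANOVA group main effect | (0 + d + d)/3 = 2d/3 | (1 + 2r)/3 |
| 12-month value adjusted for baseline | d | 1 − r² |
| Mean of both follow-ups adjusted for baseline | d | (1 + r)/2 − r² |

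The group-by-time test uses an F distribution on 2 and 252 degrees of freedom. The squared deviations of (0, d, d) about their mean sum to 2d²/3, so the noncentrality is (n/2)(2d²/3)/(1 − r). At d = 0.5 and r = 0.5 this is 32 × 0.1667/0.5 = 10.67.

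**Step 3: power at d = 0.5.** The main effect is 2 × 0.5/3 = 0.33 SD.

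| Test | r = 0.3 | r = 0.5 | r = 0.7 |
|---|---|---|---|
| 12-month t-test, no baseline | 80% | 80% | 80% |
| ANOVA group main effect | 73% | 63% | 55% |
| ANOVA group-by-time | 69% | 84% | 97% |
| Baseline-adjusted, 12 months | 84% | 90% | 98% |
| Baseline-adjusted, mean of follow-ups | 96% | 98% | 99.7% |

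At r = 0.8 the main effect has 52%. Group-by-time (99.8%) is then level with the 12-month adjusted analysis (99.7%), while the adjusted follow-up mean is at essentially 100%.

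**Step 4: total cholesterol on the plan's own SD.** 0.5/0.7 = 0.71 SD. At that effect the diluted main effect has about 95%, 91% and 85% power at r = 0.3, 0.5 and 0.7.

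**Step 5: dropping incomplete cases.** 72 × 0.9 = 64.8 per arm, which gives 81% for the planned comparison at 0.5 SD (normal approximation). So the budgeted loss alone does not breach the plan. If, as an assumption, a further 5% or 10% miss only the 3-month value, complete cases are 64.8 × 0.95 = 61.6 or 64.8 × 0.90 = 58.3. Power for the same comparison is then 79% or 77%.

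**The case against.** **Power depends on the term and on r.** The plan does not say that the main effect is the treatment test, and in a pre/post design group-by-time is the usual choice. That test meets the planned 80% from a correlation of about 0.5. A reader might infer that the trial is underpowered as planned, and the documents do not support that: neither the term nor the correlation is stated, and for total cholesterol even the diluted main effect exceeds 80% at r = 0.3 to 0.7. What stands is the efficiency loss. The baseline-adjusted follow-up mean has more power than either ANOVA term at every correlation tried.

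**Baseline as a response is inferred.** This is true, and it is why the point rests on the natural reading. No covariate is named that would suggest another.

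**Intention-to-treat.** A reader might infer that the method contradicts the stated principle. It does not strictly do so: intention-to-treat also means analysis as allocated, no deletion rule is written, and imputation is not excluded and may be described in a document not shown. Tension remains, because the classical form of the named method would analyse completers only.

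**Loss of sample and bias.** A reader might assume 5% to 10% of blood samples missed at each of three visits and arrive at about 55 to 47 complete cases per arm. No such rate is given, that count includes missed baseline samples, and the 10% loss is already in the 72. A reader might also infer differential missingness, because participants "will visit the clinics by their own arrangement" and only the modular arm is coached. Nothing in the documents shows that missingness would differ by arm, or in which direction.

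**Conclusion.** The point holds as a matter of efficiency and of use of the randomised sample. If baseline is a response level, the group main effect shrinks a constant 0.5 SD effect to 0.33 SD and falls short of the planned 80% at every correlation tried. Group-by-time avoids that dilution but reaches 80% only from a correlation of about 0.5. At correlations of 0.3 to 0.7 both have less power than a baseline-adjusted 12-month analysis, and both stay below the adjusted mean of the two follow-ups throughout.

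These figures rest on 64 completers per arm, compound symmetry, a constant effect after baseline and an assumed correlation. For total cholesterol at 0.71 SD the practical loss is smaller. Dropping participants with a missing visit takes power below plan only if intermittent missingness comes on top of the budgeted 10%. This is a worthwhile improvement to the analysis; the stated method does not make the trial invalid.

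**What to change.** For continuous outcomes, analyse the 3- and 12-month values in a likelihood-based linear mixed model with group, visit, group-by-visit and the baseline value as covariate. Alternatively, model all three visits with the baseline mean constrained equal across the two randomised arms, which also retains participants whose baseline value is missing. Include every randomised participant with any follow-up value, in the arm allocated. State the modular-minus-conventional contrast that tests the treatment effect, including whether it is taken at 12 months or over both follow-ups, and report it as an adjusted mean difference with 95% CI.

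The cost is revised wording and modest extra programming. Baseline is already collected, so no new data, visits or participants are needed.

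### The plan names chi-square or Fisher tests for within-group changes in proportions, which are paired; between the randomised arms the same tests are valid but waste the baseline data

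*Protocol article*

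**What the plan says.** The Data analysis section of the protocol article sets out the tests in one sentence. It opens with its scope and the method for continuous outcomes: "Differences in outcome measures, between and within groups, will be compared using repeated measures ANOVAs for continuous variables". For categorical outcomes it then offers a choice of χ² tests or "Fishers exact tests, as appropriate, for proportions of categorical variables". Significance is fixed next: "Two tailed p values of < 0.05 will be considered significant". No paired or repeated-measures method, and no use of the baseline value, is named for a categorical outcome.

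Under Outcome measures, the same participants are assessed three times: "At three and 12 month follow-up, all baseline measures will be repeated during face-to-face assessments by a researcher blinded to group allocation". The risk factors are listed there: "Modifiable risk factors to be measured are serum cholesterol, BP, smoking status, physical activity, overweight and depression". Smoking status is categorical, the IPAQ is scored partly as a three-level category, and the section gives cut points that turn the other factors into yes/no variables. The Discussion section makes the modifiable risk factors the primary outcomes.

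**The concern.** The scope phrase "Differences in outcome measures, between and within groups" stands ahead of both method clauses. For continuous outcomes the plan recognises repeated measurement and names a method for it. For categorical outcomes it names only tests that assume two independent samples. Applied to baseline against follow-up within one group, such a test counts each participant twice as if two people had been observed.

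At stake are the within-group p-values for smoking, activity category and any risk factor analysed by its cut point. A second, lesser loss arises between the modular and conventional care arms. Baseline status is likely to be a strong predictor of follow-up status for an outcome such as smoking. It will already have been collected, and the named test makes no use of it.

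**Working it through.** **Numbers available.** The plan gives no figure on this point, so its sample size serves only to fix the number analysed. A two-sample t-test for 0.5 SD at 80% power and two-sided 0.05 needs 63.8, so 64 per group; 64/0.9 = 71.1, so 72. The stated 72 reproduces. After 10% loss, 72 × 0.9 = 64.8, so 64 or 65 per group are used below.

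**Within a group: size of the test.** Let the true proportion p be the same at both visits, with within-person correlation ρ.
- The chi-square test assumes the difference has variance 2p(1−p)/n.
- The true variance is 2p(1−p)(1−ρ)/n.
- The test statistic therefore has standard deviation √(1−ρ) instead of 1, and the true size is 2[1 − Φ(1.96/√(1−ρ))].

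The documents give no ρ, so a range is assumed:

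| ρ | 1.96/√(1−ρ) | true size at nominal 0.05 |
|---|---|---|
| 0 | 1.96 | 0.050 |
| 0.3 | 2.34 | 0.019 |
| 0.5 | 2.77 | 0.0056 |
| 0.7 | 3.58 | 0.00035 |

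Simulation with 65 pairs and prevalence 20% to 50% (20,000 runs each) agrees: 0.018 to 0.021, 0.005 to 0.007, and 0.0003 to 0.0006 at ρ = 0.3, 0.5 and 0.7. McNemar's test stays between 0.041 and 0.056.

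**Within a group: power.** For a fall from 30% to 20% in 65 people, chi-square has power 0.18 against 0.43 for McNemar at ρ = 0.5, and 0.13 against 0.69 at ρ = 0.7.

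**Within a group: worked example (assumed counts).** Of 64 people, 20 smoke at baseline, 8 of them quit and nobody starts, so 12 smoke at follow-up.
- Chi-square, 20/64 against 12/64: difference 0.125; pooled proportion 32/128 = 0.25; standard error √(0.25 × 0.75 × 2/64) = 0.0765; z = 1.63; p = 0.102. Fisher gives p = 0.152.
- Exact McNemar, 8 changes against 0: 2 × (1/2)^8 = 0.0078.

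A less extreme case (65 pairs: 10 quit, 2 start, 10 smoke at both visits, 43 at neither) gives chi-square p = 0.10, Fisher p = 0.15 and exact McNemar p = 0.039. In both examples the conclusion changes at the plan's 0.05 threshold.

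**Between the randomised arms: validity.** With 65 per arm and no true difference, the simulated size of the follow-up chi-square is 0.045 to 0.054. The p-value is sound.

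**Between the randomised arms: power.** Every input here is an assumption, since the documents give no smoking rates: 64 or 65 per arm, 90% of control smokers still smoking at follow-up, and 2% of baseline non-smokers smoking at follow-up. The stratified test is Mantel-Haenszel by baseline smoking, without continuity correction.

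| smokers at baseline | modular smokers still smoking | chi-square | stratified |
|---|---|---|---|
| 30% | 50% | 37% | 70% |
| 30% | 70% | 12% | 26% to 28% |
| 20% | 50% | 23% | 47% |
| 20% | 70% | 9% | 17% |

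Across these cases stratifying by baseline roughly doubles the power.

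**The case against.** The strongest reply concerns the between-arm comparison. Allocation follows the baseline assessment and is random, so an unadjusted comparison of proportions at follow-up is legitimate and common. A reader might infer that ignoring baseline status makes the between-arm p-values wrong. The documents do not support that: under randomisation the test keeps its size, and only power is lost. A reader might also infer that the reported error bars would be wrong. That is not supported either, because the choice of test does not alter a reported mean, standard error or proportion.

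The size of the power gain can fairly be questioned. It rests on assumed rates. With smaller effects or fewer smokers, neither test has useful power. With a continuity correction, the stratified test falls to 57% in the most favourable case and to about 7% in the least favourable, no better than chi-square.

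Three points limit the within-group error. It is conservative, so false claims of change become rarer. Within-group change is not the randomised comparison that answers the trial's objective. Cholesterol, blood pressure, BMI, depression score and MET-minutes can be analysed as continuous variables, where repeated measures ANOVA takes account of the pairing. All three stand, and they limit the weight of the point.

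Finally, a journal article compresses its methods, and McNemar's statistic is itself a chi-square. But the phrase about appropriateness follows the two named tests and most naturally means the choice between them. The sentence states a rule for within-group proportions, and that rule is wrong, so this is more than detail left to a fuller document.

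**Conclusion.** The point holds for within-group change in proportions. As worded, the plan applies independent-samples tests to paired data. Whenever a person's status at one visit is positively correlated with status at another, the p-values are too large. The assumed correlations of 0.3 to 0.7 bring the true size down from 0.05 to between about 0.02 and 0.0003, with a matching loss of power to show real change.

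Between the modular and conventional care arms the named test is valid but inefficient. Power of roughly 9% to 37%, against 17% to 70% with stratification, illustrates the loss under assumed smoking rates and is not a forecast for this trial. The required sample size is unaffected, because it rests on total cholesterol. This is a correction worth making, and it does not threaten the trial's main randomised comparison.

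**What to change.** Replace the categorical clause of the Data analysis sentence with two rules.

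- **Within groups:** McNemar's test for binary outcomes, Bowker's test for the three-level IPAQ category, and Cochran's Q where a binary outcome is compared over all three visits. Label these results descriptive and draw no efficacy claim from them.
- **Between the randomised arms:** logistic regression with baseline status as a covariate, or Mantel-Haenszel stratified by baseline status. Alternatively, use a GEE or mixed logistic model over three and 12 months, in a form suited to three levels for the IPAQ category. State whether a continuity correction is used, because with few smokers it can remove the gain.

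The cost is one sentence of analysis wording. The methods are standard, the baseline data are already to be collected, and neither the sample size nor the visit schedule changes.
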